**Methods and analysis:**

A cohort study will be conducted at Zhongshan Ophthalmic Center. We plan to recruit 604 participants diagnosed with CEL and aged ≥3 years old. Patients with mild lens subluxation and stable visual conditions will be included in the non-surgical group and follow-up at 1, 2 and 3 years after enrolment. Patients with severe lens subluxation who accept CEL surgery will be included in the surgical group. Different surgical techniques, including phacoemulsification, in-the-bag intraocular lens implantation (with or without capsular tension ring) and trans-scleral fixation, will be used depending on the severity of dislocation. Patients will be followed up at 3 months, and 1, 2 and 3 years postoperatively. Over a 5-year follow-up period, patients will receive a detailed ocular examination, including optometry, biological measurement, specular microscopy, ultrasound biomicroscopy, anterior segment and posterior segment optical coherence tomography (OCT), OCT angiography, echocardiography and questionnaires on vision-related quality of life. The primary outcome is the change of best-corrected visual acuity and the incidence of complications in both groups.

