### Objective

The study is designed as a prospective clinical trial to investigate the prognosis and complications in patients with CEL with conservative and surgical management. The aim is to serve as a reference for disease management, specifically for choice of surgical timing and surgical method.

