### Preoperative management

All patients diagnosed with CEL will be followed up since the enrolment. The surgery will be performed when either of the following situations occurs: (1) BCVA <0.3 in LogMAR acuity; (2) monocular diplopia; (3) progressive subluxation of the lens affecting the pupillary axis; (4) complicated with severe cataract or secondary glaucoma or corneal endothelial decompensation or retinal detachment.^8^

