### Surgery methods management

The choice of surgical methods depends on the degree of ectopia lentis and the state of zonules. If the extent of the unhealthy zonules (broken or weak) is ≤180°, phacoemulsification and in-the-bag IOL implantation (with or without capsular tension ring) will be used. Otherwise, the capsular bag will be removed, and IOL will be fixed through trans-scleral fixation. Surgery will be performed by the same surgeon (DZ). Rayner 920H/970C or Sensar AR40e will be used as the implanted IOL.

The surgical techniques for patients who received in-the-bag IOL implantation are as follows: a 3.0 mm corneal tunnel incision will be made at 12 o’clock. Then, a continuous circular capsulorhexis will be performed manually. Iris hooks will stabilise the bag, and the lens will be aspirated with a phacoemulsifer. IOL will be implanted in the bag, and the capsular tension ring will be implanted when the IOL cannot be stably fixed.

For patients who received trans-scleral fixation of IOL, the surgical techniques will be performed as the previous study described.^8^ In brief, a 3.0 mm corneal tunnel incision will be made at 12 o’clock. Then, a continuous circular capsulorhexis will be performed manually, and the capsular bag will be removed after the phacoaspiration. Trans-scleral fixation of IOL will be performed with the two IOL haptics sutured by 8-0 polypropylene at 2.0 mm posterior to the corneal limbus. Anterior vitrectomy will be performed when severe vitreous prolapse occurs.

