### Outcome measures

#### Primary outcome

The primary outcome is the change of BCVA and the incidence of complications (time frame: non-surgical group is evaluated at the first visit and 1, 2, 3 years after enrolment; surgical group is evaluated at preoperation, 3 months, and 1, 2, 3 years postoperatively).

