### Statistical analysis plan

Statistical analysis will be performed using Stata V.15.0 (StataCorp, College Station, Texas, USA). Quantitative data conforming to a normal distribution will be described as the mean±SD. The difference between the baseline and follow-up data will be compared by one-way analysis of variance. The median±IQR will describe the quantitative data of the skewness distribution. The Wilcoxon signed-rank test will be used to compare these data’s differences. For qualitative data described as proportions, the Χ^2^ test or Fisher’s exact test will be used to compare the differences between groups. P<0.05 is considered statistically significant. The differences and 95% CI in the changes of BCVA and other parameters will be calculated. The univariable linear regression model will estimate these changes and their associated factors. All variables with p<0.05 in the univariable regression analysis will be included in the multivariable linear regression model.

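### Severity decides who has surgery and by which technique, yet complications are compared between groups without adjustment and BCVA covariates are chosen by a univariable P<0.05 screen

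*Protocol article*

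**What the plan says.** All references are to the protocol article.

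- **Cohort.** The abstract's Methods and analysis: "Patients with mild lens subluxation and stable visual conditions will be included in the non-surgical group", while "Patients with severe lens subluxation who accept CEL surgery will be included in the surgical group".
- **Trigger.** Preoperative management follows everyone from enrolment and operates when any one of four situations arises. The list opens: "The surgery will be performed when either of the following situations occurs: (1) BCVA <0.3 in LogMAR acuity". The others are monocular diplopia, progression that affects the pupillary axis, and serious complications of the disease.
- **Technique.** Surgery methods management: "The choice of surgical methods depends on the degree of ectopia lentis and the state of zonules". Unhealthy zonules over at most 180° lead to in-the-bag implantation, a larger extent to trans-scleral fixation.
- **Purpose.** The Objective section wants a reference for disease management, "specifically for choice of surgical timing and surgical method".
- **Primary outcome.** "The primary outcome is the change of BCVA and the incidence of complications".
- **Analysis.** The Statistical analysis plan section gives proportions a chi-square test or Fisher's "exact test will be used to compare the differences between groups". The only regression named is linear, for changes in BCVA and other parameters, and covariates enter it by this rule: "All variables with p<0.05 in the univariable regression analysis will be included in the multivariable linear regression model".

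No severity variable is fixed in any model. Confounding by severity is not among the listed limitations.

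**The concern.** Patients reach the surgical group because their disease is worse, and reach trans-scleral fixation because their zonules are worse. If worse disease also carries more complications, a crude test of proportions picks that up whether or not management matters. Complication incidence is a primary outcome, and no adjusted model is stated for it.

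Two features add to this. The surgical group has a 3-month visit that the other group lacks, so it has one more occasion on which complications are collected. Patients can also move from observation to surgery, which makes time at risk under each form of management unequal. Some surgical triggers (secondary glaucoma, endothelial decompensation, retinal detachment) could themselves be counted as complications; the article does not say.

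For BCVA change, a significance screen is a poor way to choose confounders. It asks whether a variable predicts outcome on its own, not whether it helped decide the group. At stake is whether a small P value on a primary outcome is read as evidence on timing or method when it may reflect who was selected.

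**Working it through.** **The plan's own figure.** With P = 0.15 and E = 0.15 × 0.20 = 0.03 (Sample size section), n = 1.96² × 0.15 × 0.85 / 0.03² = 544.2, and 544/0.9 = 604.4. Both stated figures, 544 and 604, reproduce. They size the precision of one overall proportion, not a contrast between groups.

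**Complications: crude test with no effect of management.** From the protocol: 544 evaluable, 15% overall risk, two-sided 5%. Assumed: the severe share s, the severe-to-mild risk ratio RR, and groups that coincide with severity.

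- Mild risk p_m = 0.15 / [(1−s) + s·RR]; severe risk p_s = RR·p_m.
- Rejection ≈ Φ[(p_s − p_m − 1.96·SE0)/SE1], where SE0 uses the pooled 15% and SE1 the separate risks.

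Example with s = 0.5 and RR = 1.5: risks are 12% and 18%, with 272 per group. SE0 = √(2 × 0.15 × 0.85/272) = 0.0306 and 1.96 × SE0 = 0.060. That equals the difference, so rejection is about 50%.

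| Severe share | RR 1.25 | RR 1.5 | RR 2 |
|---|---|---|---|
| 30% | 18.8% | 49.7% | 91.2% |
| 50% | 19.2% | 50.0% | 90.6% |
| 70% | 14.8% | 37.5% | 77.9% |

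The nominal rate is 5%. Looser alignment weakens the effect. If the surgical group is 80% severe and the other 20% severe, with risks of 20% and 10%, the group risks are 0.8×0.20 + 0.2×0.10 = 18% and 0.2×0.20 + 0.8×0.10 = 12%. Rejection is then about 50% rather than 91%.

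**BCVA change: the P<0.05 screen.** Everything here except N = 544 is assumed. Severity S is standard normal, a patient is surgical if S plus noise of SD 0.5 exceeds 0, and change = β·group + γ·S + error of SD 1. Results come from 2,000 replicates.

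| β | γ | Severity dropped | Bias, screen | Bias, prespecified | Rejection, screen | Rejection, prespecified |
|---|---|---|---|---|---|---|
| 0 | 0.3 | 0% | −0.01 | −0.01 | 5.1% | 5.1% |
| 0 | 0.1 | 36% | 0.03 | 0.00 | 6.5% | 5.1% |
| 0.3 | −0.2 | 43% | −0.10 | 0.00 | 42% | 69% |
| 0.5 | −0.3 | 21% | −0.07 | 0.00 | 86% | 98% |
| 0.6 | −0.4 | 2% | −0.01 | 0.00 | 99% | 99.8% |

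The third row can be seen directly. The univariable slope on S is γ + β·cov(group, S), with cov = 0.399/√1.25 = 0.357. That gives −0.2 + 0.3 × 0.357 = −0.093. Its standard error is about 1/√544 = 0.043, so the expected z is about 2.2, barely beyond 1.96, and severity is lost in roughly four studies in ten.

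The simulation kept group in the model whatever its P value. If group is itself screened, as the wording permits, row three is worse: its crude test was significant in only 4.6% of replicates.

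**The case against.** The best defence is that this is a descriptive cohort. The sample size targets one overall proportion, the abstract asks for outcomes in both groups, the stated comparison of quantitative data is baseline against follow-up, and no technique comparison is spelled out. That reading is available. The same article, however, tests proportions between groups and wants the results to guide timing and method, so the reader needs to be told how far those tests go. An unseen full analysis plan does not remove the point, because the crude test and the screen are rules the article states.

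Some stronger readings are tempting but not supported:

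- **That all group contrasts mainly measure severity.** The documents give no severity-specific risks. For BCVA some adjustment is planned, and it works when severity strongly predicts outcome (first row of the BCVA table).
- **That a significant difference is to be expected without any effect.** This depends on the risk ratio; at 1.25 rejection is 15-19%.
- **That BCVA gains in the surgical group reflect regression to the mean.** BCVA is one of four alternative triggers. It is printed as below 0.3 LogMAR, which taken literally means better acuity, so the direction of selection cannot be settled from the text.
- **That every confounder is already measured in both groups.** Secondary outcomes times genetic state only before operation, although Examinations sequences each subject, and the limitations say subtypes may not be classified.
- **That counting events only at shared visits cures the visit imbalance.** It could hide early surgical complications that resolve before year 1.

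**Conclusion.** The point holds. As written, the crude complication contrast is confounded by severity, and no adjusted alternative is stated for a primary outcome. The size is illustrative: false rejection of about 15-19%, 38-50% or 78-91% for severe-to-mild risk ratios of 1.25, 1.5 or 2, given 544 evaluable patients, 15% overall risk, a severe share of 30-70% and groups that follow severity exactly. Mixing of severity between groups would lower these figures.

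For BCVA the fault is narrower. The screen can drop a true confounder, and in the assumed scenarios the damage was material where treatment and severity effects opposed each other (bias up to 0.10 SD, power 42% against 69%). Elsewhere it was small.

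Adjustment will not turn these contrasts into effects of management. Technique follows a rule on zonular extent, and the cohort split follows severity closely, so overlap is limited in both.

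**What to change.** Change the Statistical analysis plan section as follows.

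1. Delete the univariable P<0.05 screen. Prespecify group, baseline BCVA, age, zonular extent and axial length in the BCVA-change model. Add Marfan or genetic status only if it is obtained in both groups.
2. Add an adjusted model for complications with the same covariates and time at risk. At 15% of 544 there would be about 82 events, or roughly 16 for each of the five terms.
3. Keep 3-month postoperative events in the main surgical-group report. Show a comparison restricted to common visits only as a sensitivity analysis.
4. Classify patients who move from observation to surgery by time-varying management status.
5. Report complications and BCVA by technique within each indication.
6. State that surgical versus non-surgical and technique contrasts are descriptive, have limited overlap in severity, and do not estimate the effect of management.

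Baseline BCVA, zonular extent and axial length are already scheduled at the first or preoperative visit, and age follows from date of birth, so no patients or visits are added. Items 2 and 4 need dates of surgery and of events, which the article does not mention and the case report form should be checked for. The price is a few degrees of freedom and a more modest claim on choice of timing and method.

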### Study monitoring

Clinical examiners will regularly check each patient’s informed consent and eligibility to ensure that all CRFs are correct and in accordance with the original data. All errors and omissions should be recorded and corrected. The examiner should ensure every participant’s withdrawal and loss of follow-up are recorded and explained in CRF, and all adverse events are recorded. The surgical operations in this project are standard methods and do not pose significant risks. The principal risks include general anaesthesia adverse effects and adverse drug reactions. This cohort study will be conducted under the guidance of the ethics committee of the Zhongshan Ophthalmic Center.

### Patient and public involvement

Neither the patients nor the public are involved in our research’s design, conduct, reporting or dissemination plans.

### Ethics and dissemination

Ethics approval was obtained from the ethics committee of the Zhongshan Ophthalmic Center (number: 2022KYPJ207). Signed consent will be obtained from the legal guardians of participants after they have been informed of the study workflow and their right to withdraw from the cohort study. This project has been designed following the principles of the Declaration of Helsinki.

The content of this cohort study is confidential information. Clinical records and data sets will be kept at the Zhongshan Ophthalmic Center in strict confidence and will only be assessed by the study investigators and authorised personnel. The results without personal data will be disseminated through peer-reviewed publications and conference presentations.
